## LIST OF ABBREVIATIONS AND RELEVANT DEFINITIONS

|                              |                                                                                                                                                                                                   |
|------------------------------|---------------------------------------------------------------------------------------------------------------------------------------------------------------------------------------------------|
| 1,25(OH)2D | 1,25-dihydroxy vitamin D                                                                                                                                                                   |
| 25(OH)D               | 25hydroxyvitamin D                                                                                                                                                                         |
| ABR                   | ABR form (General Assessment and Registration form) is the application form that is required for submission to the accredited Ethics Committee (ABR = Algemene Beoordeling en Registratie) |
| ALT                   | Alanine aminotransferase                                                                                                                                                                   |
| AP                    | Alkaline phosphatase                                                                                                                                                                       |
| AST                   | Aspartate aminotransferase                                                                                                                                                                 |
| AE                    | Adverse Event                                                                                                                                                                              |
| AR                    | Adverse Reaction                                                                                                                                                                           |
| CA                    | Competent Authority                                                                                                                                                                        |
| CCMO                  | Central Committee on Research Involving Human Subjects                                                                                                                                     |
| CV                    | Curriculum Vitae                                                                                                                                                                           |
| DSMB                  | Data Safety Monitoring Board                                                                                                                                                               |
| EU                    | European Union                                                                                                                                                                             |
| EDSS                  | Expanded Disability Status Scale                                                                                                                                                           |
| EudraCT               | European drug regulatory affairs Clinical Trials GCP Good Clinical Practice                                                                                                                |
| IB                    | Investigator's Brochure                                                                                                                                                                    |
| IC                    | Informed Consent                                                                                                                                                                           |
| IFN-γ                 | Interferon gamma                                                                                                                                                                           |
| IL-4                  | Interleukin 4                                                                                                                                                                              |
| IMP                   | Investigational Medicinal Product                                                                                                                                                          |
| IMPD                  | Investigational Medicinal Product Dossier                                                                                                                                                  |
| METC                  | Medical research ethics committee (MREC); in Dutch: medisch ethische toetsing commissie (METC)                                                                                             |
| MS                    | Multiple Sclerosis                                                                                                                                                                         |
| PTH                   | Parathyroid hormone                                                                                                                                                                        |
| RRMS                  | Relapsing Remitting Multiple Sclerosis                                                                                                                                                     |

|                |                                                                                                                                                                                                                                                                                                                                           |
|----------------|-------------------------------------------------------------------------------------------------------------------------------------------------------------------------------------------------------------------------------------------------------------------------------------------------------------------------------------------|
| (S)AE   | Serious Adverse Event                                                                                                                                                                                                                                                                                                              |
| SPC     | Summary of Product Characteristics (in Dutch: officiële productinformatie IB1-tekst)                                                                                                                                                                                                                                               |
| Sponsor | The sponsor is the party that commissions the organisation or performance of the research, for example a pharmaceutical company, academic hospital, scientific organisation or investigator. A party that provides funding for a study but does not commission it is not regarded as the sponsor, but referred to as a subsidising party. |
| SUSAR   | Suspected Unexpected Serious Adverse Reaction                                                                                                                                                                                                                                                                                      |
| Th1     | T helper cell type 1                                                                                                                                                                                                                                                                                                               |
| Th2     | T helper cell type 2                                                                                                                                                                                                                                                                                                               |
| Treg    | Regulatory T cell (CD4+CD25+CD127- or CD4+CD25+FoxP3+)                                                                                                                                                                                                                                                                             |
| Tresp   | Responder T cell (CD4+CD25-)                                                                                                                                                                                                                                                                                                       |
| Wbp     | Personal Data Protection Act (in Dutch: Wet Bescherming Persoonsgegevens)                                                                                                                                                                                                                                                          |
| WMO     | Medical Research Involving Human Subjects Act (Wet Medisch-wetenschappelijk Onderzoek met Mensen)                                                                                                                                                                                                                                  |

**SUMMARY**

**Rationale:** In earlier studies, we observed a positive correlation between vitamin D status and the regulation of the T cell compartment in MS patients.

**Objective:** The goal of this study is to assess whether supplementation of high doses vitamin D3 results in a promotion of T cell regulation. Meanwhile, the effectiveness in raising serum 25(OH)D levels, as well as the safety of this intervention with regard to calcium homeostasis will be monitored.

**Study design:** This is a cohort-study.

**Study population:** A total number of 15 participants will be included. These are interferon beta 1a or 1b-treated relapsing remitting MS patients older than 18 years, with a disease course shorter than 6 years. They have no disorders of the vitamin D hormonal system, or disorders which augment their susceptibility for hypercalcemia. Additionally, pregnant women will not take part in this study.

**Intervention (if applicable):** Patients will be supplemented with 500 µg vitamin D3/day in the form of Vigantol® (Merck™) solution for 12 weeks.

**Main study parameters/endpoints:** The effect of vitamin D supplementation on the T-cell compartment and in particular Treg function will be assessed. Secondly, serum 25(OH)D values, serum total calcium levels and kidney- and liver function will be monitored throughout the study.

**Nature and extent of the burden and risks associated with participation, benefit and group**

**relatedness:** Patients have to visit the hospital 6 times, donate blood 6 times, and have to use the vitamin D3 solution every day. The potential risk of hypervitaminosis D is hypercalcemia. Previous studies with high-dose vitamin D supplementation in MS found no hypercalcemia. Additionally, we exclude all patients which are potentially more sensitive for hypervitaminosis D and hypercalcemia. This study will provide valuable evidence on the effect of vitamin D on the T-cell compartment of MS patients.

## 1. INTRODUCTION AND RATIONALE

We are dependent upon our environment for acquiring vitamin D. Although a minor part is acquired by diet, most vitamin D is synthesised by exposure of the skin to sunlight. In the serum, vitamin D is predominantly present as its biologically inactive metabolite 25-hydroxyvitamin D (25(OH)D) (Hollis et al. 2007), and this metabolite is widely accepted to be the best indicator of vitamin D status (Hollis, 1996). Upon signals from calcium metabolism, 25(OH)D is further hydroxylised by the kidneys towards 1,25-dihydroxyvitamin D (1,25(OH)2D), the biologically active vitamin D metabolite. However other cell types, like T cells (Correale et al. 2009) and Macrophages (Smolders et al., 2008a), can also activate vitamin D. The balance between the different vitamin D metabolites in the serum and presumably also in the tissues is dependent upon several factors, including genetic polymorphisms of the vitamin D receptor (Smolders et al. 2009a; Smolders et al. 2009b).

An impaired vitamin D status leads to a decompensation of calcium metabolism, resulting in reduced serum calcium levels and bone mass density. 25(OH)D levels below 75 nmol/L have been proposed to be insufficient for maintaining a healthy calcium metabolism (Dawson-Hughes et al. 2005). Recent studies attribute additional roles to vitamin D in body homeostasis, especially in immune regulation. Impaired levels of vitamin D have been associated with several autoimmune diseases, including inflammatory bowel disease, systemic lupus erythematosus and multiple sclerosis (MS). We are interested in the latter association.

Low serum levels of 25(OH)D in adolescence and limited sun exposure in childhood have been associated with an increased incidence of MS (Munger et al. 2007). In MS patients, low 25(OH)D levels have been associated with increased levels of disability in the entire MS population, and with a lower chance to remain relapse free in relapsing remitting MS (RRMS) patients with a short disease duration (Smolders et al. 2008a). In the pathophysiology of MS, auto-reactive T helper type 1 (Th1) and Th17 cells and a compromised regulatory T cell (Treg) function play an essential role. *In vitro* research suggest that vitamin D skews the immune response from an inflammatory Th1/ Th17 towards an anti-inflammatory Th2/ Treg phenotype (Smolders 2008b). Interestingly, preliminary data from our study 'Vitamin D and the T cell compartment in multiple sclerosis' (NL 22666.096.07) shows that serum 25(OH)D levels correlate negatively with the IFN- $\gamma$ /IL-4 ratio, and with a better function of Treg in RRMS patients with a short disease course. These findings indicate that vitamin D modulates the T cell response towards a less inflammatory phenotype in MS patients *in vivo*. Interestingly, treatment with vitamin D can prevent and even cure animals in an experimental model of MS (Smolders et al. 2008a). Therefore, we would like to assess in the present study whether elevation of 25(OH)D levels by vitamin D3 supplementation results in the anticipated shift within the T cell compartment.

The serum 25(OH)D level which should be achieved for an optimal immune regulation is uncertain. Based on measurements of 25(OH)D levels in primates in Africa and coast guards in Israel, it has been suggested that our immune system has been designed to be exposed to 25(OH)D levels exceeding 150 nmol/L (Vieth, 2005). Recently, it was shown that the correlation between vitamin D and

25(OH)D in the serum reaches a plateau phase at 25(OH)D levels of 100 nmol/L (Hollis et al. 2007), indicating that the formation of 25(OH)D is sated at levels exceeding 100 nmol/L. Furthermore, adolescents with serum 25(OH)D levels >100 nmol/L were found to have a reduced risk for developing MS in later life, compared to adolescents with the lowest serum 25(OH)D values (Munger et al., 2006). With vitamin D therapy in this study, we aim for 25(OH)D levels exceeding these concentrations. In our recent study 'Vitamin D and the T cell compartment in multiple sclerosis' (NL 22666.096.07), 50% of RRMS patients with a short disease course had 25(OH)D levels <50 nmol/L, and only 3 patients exceeded the 100nmol/L. Interestingly, these three patients had all an optimal Treg function. These figures suggest that, when supplementing vitamin D in an attempt to modulate the immune response, vitamin D levels should exceed at least 100-150 nmol/L.

To determine the dose of vitamin D3 to reach these levels, one has to take safety into account. The only potential side effect of vitamin D supplementation, is decompensation of calcium metabolism and elevation of serum calcium values (hypercalcemia). Hypercalcemia has been rarely described in vitamin D3 supplemented subjects (Hathcock et al. 2007). The issue of safety will be specifically addressed in section 5.3. Two studies did assess the effect of vitamin D3 supplementation on 25(OH)D levels in MS patients. One study provided in weekly boluses the equivalent of 1000 µg/d, and reached a mean level of 325 nmol/L (min-max range 200-800 nmol/L) (Kimball et al. 2008). Another study supplemented patients with 250 µg/d for one year, reaching mean 25(OH)D levels of 413 nmol/L (min-max range 66 – 729) (Burton et al., 2008). Since we want to elevate 25(OH)D levels in all our patients at least above 100-150 nmol/L, we want to supplement our cohort with 500 µg/d. In several studies with vitamin D, it takes about 3 months for serum 25(OH)D levels to reach a new plateau phase. Therefore, subjects will receive 12 weeks supplementation.

To summarize, we would like to supplement a small cohort of RRMS patients, treated with interferon beta 1a or 1b, with a short disease course (<5 years) with high doses of vitamin D3 in an open label design. The main goal is to determine whether this dose is effective in modulating the T cell compartment. The primary outcome measure will be improvement of Treg function in proliferation suppression assays. Furthermore, specific safety issues will be assessed. Does an acute start with high doses vitamin D3 provoke side effects? Is calcium metabolism well regulated? Are serum 25(OH)D also effectively elevated in these patients using interferon beta 1a or 1b? The latter question is highly relevant, since therapy with Interferon Beta 1a and 1b specifically inhibits the superfamily of cytochrome P450 enzymes, to which the vitamin D hydroxylating enzymes also belong.

In MS, T cell regulation has been shown to be impaired. At present, disease modulating drugs in MS, like Beta Interferons, promote T cell regulation. The positive correlation between vitamin D status and T cell regulation that we observed in our previous study suggests that elevation of vitamin D status might result in promotion of T cell regulation. It is tempting to speculate that this promotion of T cell regulation might result in a subsequent amelioration of MS. Therefore, this study will be an important step towards assessment of vitamin D therapy in MS.

## 2. OBJECTIVES

Primary Objective:

- Does vitamin D3 supplementation with a dose of 500 µg/ day for 12 weeks result in an improved regulatory T cell function (i.e. reduction of ED50 in the *in vitro* assay) in relapsing remitting MS patients treated with interferon beta?

Secondary Objective(s):

- Does vitamin D3 supplementation with a dose of 500 µg/ day for 12 weeks result in a shift of the T cell compartment from a Th1 to a Th2 response in relapsing remitting MS patients treated with interferon beta?
- Is supplementation of vitamin D3 with a dose of 500 µg/ day for 12 weeks effective in raising 25(OH)D levels above 100 nmol/L in relapsing remitting MS patients treated with interferon beta?
- Is supplementation of vitamin D3 with a dose of 500 µg/ day for 12 weeks safe and tolerable in relapsing remitting MS patients treated with interferon beta?

### 3. STUDY DESIGN

The study will be a cohort study in 15 RRMS patients with a short disease course who are treated with interferon beta 1a or 1b. In this single study arm, vitamin D will be supplemented as a commercially available oil-based vitamin D3 solution (Vigantol®, Merck™) at a dose of 500 µg/ day for 12 weeks. Four weeks after termination of vitamin D3 therapy, biochemical markers will be checked to ensure normalization. See the flow-chart below (time indicated in weeks). This will be discussed in detail later.

[figure not shown]

## 4. STUDY POPULATION

### 4.1 Population (base)

The patient cohort of the study will be collected from MS patients visiting our outpatient clinic, and from the patients which were included for the study 'Vitamin D and the T cell compartment in multiple sclerosis' (NL 22666.096.07) and indicated on their informed consent form that they would like to be invited to take part in future studies on vitamin D and MS (about 25 Beta Interferon users).

All subjects who are potentially more sensitive to develop hypercalcemia or complications from an eventual hypercalcemia (according to Hathcock et al. 2007) will be excluded to take part in this study (see exclusion criteria). A standard case report form (CRF) will be used to assess these issues at inclusion, with the additional performance of an ECG.

### 4.2 Inclusion criteria

Inclusion criteria for the patient cohort are:

- Relapsing Remitting MS clinical phenotype (Revised McDonald criteria 2005)
- Disease duration from MS onset (first symptoms attributable to MS) < 6 years.
- At start of study > 6 weeks in clinical remission of disease
- Use of Interferon beta (1a or 1b) as immune modulation.
- Age > 18 years.

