### 4.3 Exclusion criteria

Exclusion criteria are:

- Progressive phenotype of MS
- Relapse (treated or untreated with steroids) < 6 weeks before start study.
- Abnormalities of vitamin D hormonal system other than low dietary intake or limited sun exposure (i.e. Malabsorption, Cirrhosis, Nephrotic syndrome, Hyperthyroidism, Renal failure, Rickets, hypoparathyroidism, known malignancy, granulomatous disorders (TB, Sarcoidosis, Silicosis), and lymphomas)
- Intake of drugs that influence vitamin D homeostasis other than corticosteroids (i.e. Orlistat and anticonvulsants).

- Conditions associated with an increased susceptibility for hypercalcemia (known arrhythmia or heart disease, treatment with digitalis or hydrochlorothiazide, and those who suffer from nephrolithiasis).
- Frequent use of tanning bed (> 1 time/week).
- Alcohol or drug abuse
- Pregnancy or the intention to become pregnant during the study period.

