### 5.2 Use of co-intervention

Patients who take part in this study are treated with interferon beta 1a (Rebif®) or Interferon Beta 1b (Betaferon® or Avonex®) and have to continue this treatment. When taking multivitamin supplements, they can be continued when the incorporated amount of vitamin D does not exceed 5 µg/day. Excessive eating of products which contains lots of calcium (dairy products) or vitamin D (fat fish and cod liver oil, in lesser amounts meat, eggs, dairy products, avocado) should be discouraged. As part of the routine visits at week 1, 6 and 12, the calcium and vitamin D intake will be inventoried. Also, the amount of sunlight exposure and recent sun-vacations will be assessed. In case of a relapse of MS during the study period, this can be normally treated with corticosteroids.

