### 6.2 Randomisation, blinding and treatment allocation

This pilot study has only one arm. All participants receive the same intervention and are not randomised.

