### **8.2 Univariate analysis**

The effect of the intervention on T cell characteristics (primary outcome measures) will be expressed as the difference between the respective continuous variables (ED50, T cell subsets or Th1/Th2 ratios) before and after treatment. The significance of this difference will be tested with a paired non-parametrical test (Wilcoxon ranking test). The same holds for the effect of the intervention on safety parameters and vitamin D metabolite values.

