### **8.3 Multivariate analysis**

No multivariate analysis will be performed.

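### Any current interferon user may enter, with no minimum time on unchanged treatment, so an early interferon effect could be read as a vitamin D effect in this one-arm comparison

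*Protocol*

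**What the plan says.** **Design and test.** Protocol section 6.2 states: "This pilot study has only one arm". Section 8.2 expresses the effect as the difference in ED50 before and after treatment and tests it with a paired Wilcoxon test. Section 8.3 adds: "No multivariate analysis will be performed".

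**Interferon.** The criterion in section 4.2 is "Use of Interferon beta (1a or 1b) as immune modulation". Section 5.2 requires the treatment to be continued, but neither section says how long it must have been in place or unchanged. The Introduction states that "disease modulating drugs in MS, like Beta Interferons, promote T cell regulation".

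**Source of patients.** Section 4.1 counts about 25 interferon users among earlier-study participants willing to be invited, and also draws on the outpatient clinic. Section 9.2 says recruitment is primarily from the earlier study, with matching patients from outside it also approached.

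**Relapse.** Section 4.2 requires more than 6 weeks of clinical remission at the start, and section 4.3 excludes "Relapse (treated or untreated with steroids) < 6 weeks before start study". For the treatment period, section 5.2 says: "In case of a relapse of MS during the study period, this can be normally treated with corticosteroids". Section 6.4.1 does not list relapse or steroid use as a reason for withdrawal, and section 6.3 sets no relapse-free interval before the week-12 sample.

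**The concern.** With one arm and no adjustment, anything that changes ED50 between baseline and week 12 becomes part of the estimated vitamin D effect. Eligibility and sampling conditions are then the main protection against other causes of change.

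The protocol names one such cause itself: interferon beta acts on T cell regulation. In a patient long established on an unchanged product, that influence should be in both samples and largely cancel in the difference. In a patient who started or switched shortly before baseline, part of it may appear only at week 12. ED50 would fall, and the fall would count as benefit. The wording of 4.2 admits such a patient.

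Section 9.4 says an effect on the T cell compartment would be an essential argument for studying vitamin D as a treatment, so a false positive would have consequences.

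A smaller asymmetry concerns relapse: the baseline sample is protected by a 6-week rule and the week-12 sample is not.

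**Working it through.** **Inputs from the protocol.** n = 15; two-sided alpha 0.05; between-patient SD of ED50 0.5503; hoped-for difference 0.7912 (all section 4.4). The n follows from the arithmetic printed there: 7.84 × 1.93502 = 15.17, about 15. The protocol gives no figure for an interferon effect on ED50, so there is no stated figure to reproduce on this point.

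**Assumptions, not in the protocol.**
- The true vitamin D effect is zero.
- m of the 15 patients have an ED50 fall due to recent interferon. The fall is 0.40, or 0.79 (the whole effect hoped for from vitamin D).
- The SD of the within-patient change is SD × √(2(1 − r)), where r is the baseline to week-12 correlation. With r = 0 it is 0.5503 × √2 = 0.778; with r = 0.5 it is 0.5503; with r = 0.75 it is 0.5503 × √0.5 = 0.389. The range used is 0.39 to 0.78.

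**Bias in the mean change** = (m / 15) × fall. For m = 3: 3/15 × 0.40 = 0.08 and 3/15 × 0.7912 = 0.158. For m = 5: 0.133 and 0.264.

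**Effect on the test.** Normally distributed changes were simulated and tested with the exact two-sided paired Wilcoxon test. Ranges run over the SD of change:

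| Affected patients (of 15) | Rejection, fall 0.40 | Rejection, fall 0.79 |
|---|---|---|
| 0 | 4–5% | 4–5% |
| 1 | about 5% | about 5% |
| 2 | 5–6% | 6–7% |
| 3 | 6–8% | 8–13% |
| 5 | 8–16% | 16–32% |

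With no affected patient, about 2% of trials show a significant improvement, which is roughly half of all rejections. With 3 or more affected, nearly all rejections are in the direction of benefit.

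**Relapse before week 12.** For an assumed relapse rate of 0.3 to 0.8 per year, the chance of a relapse in the last 6 weeks is 1 − exp(−rate × 6/52), or 3.4% to 8.8% per patient. Times 15, this is 0.5 to 1.3 patients; the chance of at least one is 41% to 75%. These count all relapses, treated with steroids or not. In the table, one shifted pair leaves two-sided rejection at about 5%.

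**The case against.** The strongest reply is that few recent starters are likely. About 25 interferon users from the earlier study are available for 15 places, and someone already on interferon in that study is unlikely to have just begun it. This stands, and it makes the lower rows of the table less plausible. It does not close the gap: outside patients may enter, and earlier participation does not establish that interferon has been unchanged since.

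Second, the protocol says that interferons promote T cell regulation but gives no size or time course for ED50. This also stands. A reader might infer that a recent starter is bound to improve over 12 weeks, or that the false-positive rate here is 20% or 30%. The document supports neither. Nothing in it suggests 5 recent starters, and 0.79 credits interferon with the full effect hoped for from vitamin D.

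Third, a single arm is a declared choice for a pilot, and section 5.2 requires interferon to continue. Both are accepted. No control arm is asked for, and continuation during the study does not settle when treatment began.

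Fourth, a reader might infer that steroid-treated relapses seriously distort the week-12 result. About one pair is affected under the assumed rates, the direction is unknown, and the test's error rate stays near nominal. Keeping all pairs in the primary test is a normal choice, and a sensitivity analysis is something a statistical analysis plan may hold.

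**Conclusion.** The eligibility gap is real and belongs to the protocol: section 4.2 leaves open an influence that the Introduction names, in a design with no control or adjustment to absorb it. Any resulting bias would favour vitamin D.

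Its size cannot be fixed from the document. It depends on the number of recent starters or switchers, the ED50 fall each would show, and the within-patient correlation, none of which is given. With one or two such patients, which the recruitment source makes more likely than five, rejection stays at about 5% to 7%. It becomes material from about three patients (6–13%), and 8–32% would need five. The point deserves correction because closing it is cheap, not because a large error is shown.

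The relapse asymmetry between baseline and week 12 exists but is minor.

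A reader might also think that ED50 values from the earlier study could serve as an untreated comparison for carried-over patients. The document does not support that use: it does not give the interval between the studies, the season or each patient's interferon status at the earlier sample, or say that the two data sets can be linked.

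**What to change.** **Section 4.2.** Require a stated minimum period on an unchanged interferon product and dose before the baseline sample. The sponsor should set the length; a period at least as long as the 12-week observation window is one example. Record the interferon start date at inclusion, and any change of product or dose during the study.

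**Section 8.2, optional.** Repeat the ED50 test without pairs in which a relapse occurred in the 6 weeks before the week-12 sample, mirroring the baseline rule in 4.2 and 4.3. The primary test keeps all pairs. Treatment of relapses is not affected.

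**Cost.** One eligibility line, a start date and a change record per patient. The pool of about 25 earlier-study users shrinks slightly, and hardly at all if most are established users. The optional analysis would lose about one pair.
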